## Abstract

Vitamin D deficiency can escalate prematurity bone disease in preterm infants and negatively influence their immature immunology system. Infants born at 24 + 0/7 weeks to 32 + 6/7 weeks of gestation will be considered for inclusion. Cord or vein blood samples will be obtained within 48 h after birth for 25-hydroxyvitamin D level measurements. Parathyroid hormone and interleukin-6 levels will be measured. Infants will be randomized to the monitored group (i.e., an initial dose of 1000 IU/day and possible modification) or the controlled group (i.e., 250 IU/day or 500 IU/day dose, depending on weight). Supplementation will be monitored up to a postconceptional age of 35 weeks. The primary endpoint is the percentage of infants with deficient or suboptimal 25-hydroxyvitamin D levels at 28 ± 2 days of age. 25-Hydroxyvitamin D levels will be measured at postconceptional age 35 ± 2 weeks. Secondary goals encompass assessing the occurrence of sepsis, osteopenia, hyperparathyroidism, and interleukin-6 concentration. The aim of this study is to evaluate the efficacy of monitored vitamin D supplementation in a group of preterm infants and ascertain if a high initial dosage of monitored vitamin D supplementation can decrease the occurrence of neonatal sepsis and metabolic bone disease.

## 1. Introduction

The well-established significance of vitamin D (vit D) in preserving skeletal health is widely recognized [1,2]. The identification of vit D receptors in various tissues and cells has offered fresh perspective on its biological effects [2]. Maintaining calcium and phosphate homeostasis is one of the key tasks for the proper functioning of the fetus and infant organism. Serum calcium and phosphorus levels are under hormonal control of the interdependent parathyroid hormone (PTH; secreted by the parathyroid glands), vit D (the active metabolite 1,25-dihydroxycholecalciferol is formed in the kidneys), phosphate (secreted by the bones), and, to a lesser extent, calcitonin (produced by the parafollicular thyroid) [3]. Parathormone (PTH)-like peptides, PTH, and calcitriol have a basic regulatory role in active transplacental calcium transport. After birth, the calcium concentration decreases in the blood; therefore, the PTH concentration increases, which stimulates the reabsorption of calcium in the kidneys and inhibits the reabsorption of phosphorus [3,4]. Furthermore, the increased synthesis of calcitriol promotes the active absorption of calcium and phosphorus from the intestines. However, in preterm infants, intestinal absorption is compromised, and human milk proves inadequate as a source of calcium and phosphorus during this developmental stage [5,6].

Research has indicated that neonatal vit D storage at birth, whether it be a full-term or preterm infant, depends on the maternal 25-hydroxyvitamin D [25(OH)D] concentration because a developing fetus obtains all of its vit D from the mother [7,8]. Deficient levels of vit D in pregnant women are linked to inadequate levels in their premature newborns (with a strong correlation, *p* value < 0.01) [9]. Vit D holds importance during pregnancy and lactation. Premature neonates miss the crucial phase of maximum mineral accretion occurring in the final trimester of pregnancy, during which 60% and 80% of whole-body calcium and phosphorus, respectively, are actively transferred from the mother to the fetus [10]. This coincides with a significant exponential rise in bone formation between 24 weeks’ gestation and term. Inadequate postnatal Ca, P, and vit D supplementation can lead to metabolic bone disease (MBD) of prematurity. MBD increases the risk of death by three times and extends hospitalization time by 40% [11]. Zung et al. conducted a prospective study in 2020, which showed that only 24% of infants had sufficient levels of 25(OH)D after birth. They suggested supplementation with at least 600 IU/day of vit D for premature newborns and infants with low birth weight to achieve increased levels of 25(OH)D before discharge [12].

Scientific societies unanimously recommend vit D supplementation in neonatal patients, as well as in pregnant women. The guidelines from the American Academy of Pediatrics (2013) suggest supplementation of 200–400 IU/day (depending on the weight) for enterally fed preterm infants [13]. In line with the latest recommendations from the European Society for Paediatric Gastroenterology, Hepatology, and Nutrition, vit D supplementation for preterm infants should range from 400 to 700 IU/kg/day, with a maximum daily dose capped at 1000 IU/day [14]. The argument for a higher dosage is the prevalence of a commonly occurring deficiency in pregnant women. In addition, the effect on the pleiotropic action of vit D in infants is observed at a concentration of 25(OH)D >30 ng/mL [7,14]. According to Polish guidelines, for neonates born at <33 weeks of gestation, if enteral nutrition is feasible, a dosage of 800 IU/day (20 µg/day) of cholecalciferol is recommended during the initial month of life, irrespective of the feeding method [7]. Dietary intake calculations should commence in the second month of life. Monitoring of supplementation is advised through serum 25(OH)D concentration assays, conducted during hospitalization (with the initial assessment after 4 weeks of supplementation) and/or follow-up in outpatient care. Caution is advised as a total daily cholecalciferol dose >1000 IU (i.e., 25 µg/day) may pose a risk of vit D overdose, particularly in neonates with a birth weight <1000 g.

A previous study [15] conducted in the Department of Neonatology and Neonatal Intensive Care at the Medical University of Warsaw (Warsaw, Poland) showed that approximately 45% of patients had suboptimal and deficiency levels at 4 weeks of age on the initial supplementation of 500 IU. Infants were randomized to receive monitored supplementation (with the option of dose modification, based on 25(OH)D levels, as per protocol) or to receive standard therapy (i.e., 500 IU) for up to 52 weeks of postconceptional age (PCA). However, monitoring has been proven to avoid overdosing during further follow-up. The quantitative ultrasonography assessment of average bone mass did not differ between the two groups of patients, but the initial dose was the same in both groups.

Vit D also has an important role in immunoregulation in the pediatric population [16]. In contrast to the immune system of full-term infants, the immune system of preterm infants exhibits several notable differences. These include a reduced population of monocytes and neutrophils, compromised effectiveness of these cells in eliminating pathogens, and diminished cytokine production. Consequently, there is a restricted capacity for T cell activation, leading to a decreased ability to combat bacterial infections and identify viruses within cells [14,15]. These abnormalities can contribute to the development of late-onset sepsis, a prevalent and serious condition in neonatal intensive care units. The frequency of late-onset sepsis is linked to the level of prematurity, exhibiting geographical variations ranging from 0.61% to 14.2% among hospitalized newborns [17]. The incidence of sepsis is significantly higher (8–20%) in premature infants and in infants with low birth weight (i.e., <1000 g) [18]. The rapid progression of the disease may lead to secondary organ damage. Early treatment is needed, which is very difficult and challenging to achieve in clinical practice. The overall mortality rate of late-onset sepsis is 2% to 20% [18]. The aim of this study will be to assess the effectiveness of monitored vit D supplementation in a population of preterm infants and to identify whether proper vit D supplementation in preterm infants can reduce the incidence of neonatal sepsis and metabolic bone disease.

## 2. Materials and Methods

### 2.1. Study Design

We are implementing an unblinded, parallel-group, randomized controlled superiority trial. Parents of neonates born between 24 + 0/7 weeks and 32 + 6/7 weeks of gestation will be offered the opportunity to participate in the study within the first 24 h of the infant’s life. After providing information orally and in writing concerning the study, we will seek written consent from the parents for the neonate and mother to participate in the trial. To enhance the relevance of the research findings, we will stratify the study group by gestational age into 24–28 and 29–32 weeks of gestation subgroups. We have planned to recruit for the study for 36 months, from September 2024 to the end of 2027. The study protocol has been registered at ClinicalTrials.gov (identifier: NCT06199102). Please see Table 1 for all planned patient-related activities.

### 2.2. Setting and Participants

All infants admitted to the Department of Neonatology and Intensive Care at the Medical University of Warsaw (Warsaw, Poland) and born at 24 + 0/7 weeks to 32 + 6/7 weeks of gestation will be considered for inclusion. Our tertiary perinatal center has an annual number of births of approximately 2500 infants, including an average of 80 infants aged <33 weeks of gestation. 25(OHD) neonatal birth concentration strongly correlates with pregnant vit D supplementation. According to the Polish Society of Gynecologists and Obstetricians, it is recommended to supplement vit D at a dose of 1500–2000 IU/day during pregnancy [19]. However, the available multivitamin supplements for pregnant women in Poland vary from 400 IU to 2000 IU. The parents of the infants will provide informed consent. Patients will be randomly assigned to the monitored group or the controlled group. We will collect a cord or vein blood sample within the first 48 h of life to evaluate 25(OH)D levels at birth. Blood samples will be taken simultaneously with other laboratory tests so as not to expose the newborn to additional blood donations. Additionally, the maternal 25(OH)D level and the neonatal birth levels of PTH and IL-6 will be measured. Once infants reach a daily enteral feeding volume of 30 mL/kg, they will receive an initial vitamin D dose. We will continue to monitor the supplementation until 35 weeks of PCA.

### 2.3. Inclusion Criteria

We will include all preterm infants with a gestational age of 24 + 0/7 to 32 + 6/7 born at our clinic or admitted to the intensive care unit (outborn infants need to be admitted within 48 h after delivery). Upon recruitment, caregivers are required to provide written informed consent for both the mother and her child to participate in the study.

### 2.4. Exclusion Criteria

We will exclude infants born at >32 weeks of gestation and with major congenital abnormalities or other severe congenital malformations, infants with genetic disorders (diagnosed before and after birth) deemed incompatible with survival, and infants with diagnosed cholestasis. Cholestasis is defined as direct bilirubin > 1 mg/dL (>17.1 μmol/L) [20]. Exclusion criteria also include the lack of written informed consent and communication challenges with caregivers.

### 2.5. Randomization Criteria

Following the receipt of signed consent for participation from the parents of the neonates, the participants will be registered and randomized within the initial 48 h. Enrolled infants will be randomized (1:1 allocation) with a block size of six.

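### One fixed, published block size of six in an unblinded single-department trial lets staff who track allocations deduce about a quarter of them before consent

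*Protocol article*

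**What the plan says.** Five statements in the protocol article bear on this point.

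- Allocation rule (section 2.5): "Enrolled infants will be randomized (1:1 allocation) with a block size of six". There is one size, and it is published.
- Blinding (section 2.1): "We are implementing an unblinded, parallel-group, randomized controlled superiority trial".
- Setting (section 2.2): candidates are infants admitted to a single department in Warsaw, with a flow described as "including an average of 80 infants aged <33 weeks of gestation" per year.
- Order of events (section 2.5): "Following the receipt of signed consent for participation from the parents of the neonates, the participants will be registered and randomized within the initial 48" hours. Screening and consent therefore come before allocation. Section 2.4 leaves some judgement at that stage: "Exclusion criteria also include the lack of written informed consent and communication challenges with caregivers".
- Strata (section 2.1): "we will stratify the study group by gestational age into 24–28 and 29–32 weeks of gestation subgroups". Section 2.5 does not say whether the randomisation list itself is divided in this way.

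The article mentions neither varying nor undisclosed block sizes. It does not say who generates or holds the list, or who carries out the randomisation. In a condensed article that silence is not a fault, and nothing below depends on it.

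**The concern.** Permuted blocks keep the arms balanced by forcing the end of each block. Where treatment is open, past allocations are visible on the ward. With one known block size, the places left in the current block can be counted from them. A centrally held, well concealed list gives no protection, because nobody needs to see it.

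At stake is who gets enrolled. A person who can predict the next arm could approach a family readily, hold back, or treat a communication difficulty as disqualifying, depending on the infant's apparent prognosis. The automated assay behind the primary endpoint limits bias in assessment, but it does nothing about selection before randomisation. Secondary outcomes such as sepsis and metabolic bone disease plausibly depend on how immature and ill the enrolled infants are.

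**Working it through.** **Inputs.** Block size 6 and 1:1 ratio (section 2.5); no blinding and two gestational-age groups (section 2.1); total N = 130 (section 2.12). The protocol gives no figure for predictability, so there is none to reproduce. The split between strata is not given; 65/65 and 50/80 are assumed.

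**Step 1: one block of six.** There are C(6,3) = 20 equally likely sequences. An allocation is certain once one arm has used its three places.

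- Positions 1 to 3: never certain.
- Position 4: certain if the first three are alike, 2/20 = 10%.
- Position 5: certain if the last two are alike, 8/20 = 40%.
- Position 6: always certain.

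Expected certain allocations per block: 0.10 + 0.40 + 1.00 = 1.5, and 1.5/6 = 25%. The closed form for block size 2m is 2m/(m + 1); with m = 3 it gives 6/4 = 1.5. Always guessing the arm with more places left is right for 4.1 of 6 allocations (68.3%), against 50% under simple randomisation.

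**Step 2: the planned trial size.**

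- One list of 130: 21 full blocks and 4 over. 21 × 1.5 + 0.10 = 31.6, or 24.3%.
- Two lists of 65: each has 10 full blocks and 5 over. 2 × (15 + 0.10 + 0.40) = 31.0, or 23.8%.
- Lists of 50 and 80: 8 and 13 full blocks, each with 2 over. 12 + 19.5 = 31.5, or 24.2%.

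Stratifying the list therefore changes almost nothing for someone who tracks each stratum.

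**Step 3: what varying the block size achieves.** These are simulations of two lists of 65, with sizes drawn with equal probability. The observer is the worst case: one who knows the possible sizes and remembers every allocation.

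| Block sizes | Certain | Best-guess hit rate | Predictable with probability 80% or more |
|---|---|---|---|
| 6 only | 24% | 0.68 | 24% |
| 4, 6 | about 5.5% | 0.69 | 27% |
| 2, 4, 6 | about 4% | 0.70 | 51% |
| 4, 6, 8 | about 2.3% | 0.68 | 24% |

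For the fixed block of six the second and fourth columns agree: short of certainty, the most lopsided state is three places against one, which gives 75%.

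Sizes 4, 6 and 8 thus remove most of the certainty, from about 31 allocations to about 3 of 130. Against an observer who knows the sizes, they leave the hit rate and the share of strong predictions where they were. A set that includes size 2 roughly doubles the share of strong predictions.

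**The case against.** A fixed permuted block is a valid method of allocation, and the protocol contains no contradiction or miscalculation here. Three further points carry weight.

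*The remedy can be oversold.* A reader might infer from the fall from 25% to 2% that varying the sizes makes allocation unpredictable. Step 3 shows otherwise. Someone willing to act on certainty would plausibly also act on 80% probability, and that share does not fall for an observer who knows the sizes. This objection stands. The benefit is the loss of certainty plus whatever non-disclosure adds, and the latter is not quantified here.

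*Knowledge is possible, not shown.* A reader might infer that staff do know the next allocation, or that the department carries out the randomisation itself. The article says neither. Deduction requires someone to know the block size, where the list begins and every earlier allocation in it. This also stands, which is why the point concerns what staff could deduce.

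*The opportunity is limited.* Randomisation falls within 48 hours of birth. At about 80 eligible infants a year, and assuming random arrivals, the expected number in 48 hours is 80 × 2/365 = 0.44. The chance of at least one is 1 − exp(−0.44), about 35%. Delaying one infant in the hope of a different slot would usually fail. Not approaching a family, or excluding on communication grounds, remains possible, so the objection narrows the risk without removing it.

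**Conclusion.** The point holds as an avoidable design weakness. With the stated rule, about 24–25% of allocations (about 31 of 130) can be deduced with certainty before the next family is approached. This assumes that someone involved in recruitment tracks past allocations in the list, or in each stratum if the list is stratified. The result does not depend on how the list is concealed or on the assumed stratum split.

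It is a risk of selection at consent. The documents do not support a claim that bias has occurred. Nor do they support the tempting claim that no analysis could repair such bias: neonatal 25(OH)D at birth, maternal 25(OH)D and gestational age are all recorded, and adjusting for them could remove part of it. Selection on unrecorded features would remain.

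Rating: cheap improvement.

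**What to change.** In section 2.5, replace the phrase that names the block size with: *in randomly varying block sizes that are not disclosed to recruiting or clinical staff*. Hold the sizes in a document kept outside the department. Avoid blocks of two; sizes 4, 6 and 8 are one suitable set. Non-disclosure is an essential part of the change, because varying the sizes alone does little against an observer who knows them.

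If randomisation is stratified by gestational age, as section 2.1 suggests, generate a separate list within each stratum. If recruitment has started, apply the new rule to the remaining allocations.

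The cost is a new list, one changed sentence and a slightly larger possible imbalance at the end of recruitment. That imbalance is at most half the largest block per list: 4 infants with sizes up to 8, against 3 with blocks of six.

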#### 2.8.2. Bone Mass and Biochemical Markers of MBD

Osteopenia in preterm infants occurs in approximately 20–30% of children with a birth weight < 1500 g and in 50–60% of children with a birth weight < 1000 g [11]. We have opted to define MBD as a reduction in bone mineral content compared to the anticipated level of mineralization for a fetus or infant of similar size or gestational age. This definition is coupled with observed biochemical and/or ultrasound changes. Neonatal staff will obtain venous samples of 0.7 mL for the Ca-P metabolism tests, including serum alkaline phosphatase and phosphate levels at 35 ± 1 weeks of PCA. The measurements will be performed using the AU480 chemistry analyzer (Beckman Coulter, Brea, CA, USA), which will undergo calibration checks with suitable controls following product guidelines. The mean value of these measurements will be used for data analysis.

We decided to define MBD as serum levels of alkaline phosphatase > 500 IU and serum phosphate < 1.8 mmol/L [25]. Moreover, we intend to evaluate average bone mass through the use of quantitative ultrasound (Sunlight PREMIER 7000; BeamMed, Petah Tikva, Israel). This method, deemed safe, noninvasive, radiation-free, and user-friendly, has been proposed as a screening tool for detecting osteopenia in premature infants [25,26]. Using a compact ultrasound probe (CRB probe RoHS 900–1000 kHz) positioned along the mid-tibia, this device quantifies the speed of sound (m/s) through the axial transmission mode. However, due to significant intraindividual variation, establishing normal values becomes challenging. The measurements will be made on the tibia, with the mid-tibial shaft length determined by measuring the distance from the knee to the heel. Placing the probe over the medial aspect of the mid-shaft tibia, three speed-of-sound measurements will be conducted.

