### 2.12. Sample Size Calculations

The sample size was determined based on the primary outcome, which is defined as the count of neonates with 25(OH)D deficiency or insufficiency. A previous study conducted in our department reported an incidence of vit D deficiency or vit D insufficiency of 80% in preterm infants at birth, which was reduced with vit D supplementation to 45% at 28 ± 2 days of age. Assuming an estimated prevalence of 80% in the standard supplementation group, we chose to detect a decrease of 25% in patients with vitamin D deficiency and vitamin D insufficiency versus the control group with a power of 80% and α = 0.05 to meet acceptable recruitment rates and reach statistically significant results. Hence, 54 infants are required in each study group. Assuming a 20% loss to follow-up (due to the decision of the principal investigator, withdrawal of consent from a parent/legal guardian), the sample size has been set at 130 patients and their mothers. We believe the recruitment of patients will last approximately 3 years.

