### 2.13. Statistical Analysis

Statistical analysis will be conducted using Statistica 13.1 (StatSoft, Tulsa, OK, USA). Our intention is to conduct intention-to-treat analyses. Continuous data will be presented as means and standard deviations or as medians and ranges, while categorical variables will be expressed as proportions. Normally distributed continuous variables will undergo analysis using the Student’s *t*-test, while the Wilcoxon rank-sum test will be applied for skewed data. Categorical variables will be analyzed using either the chi-square test or Fisher’s exact test. The 95% confidence intervals (95% CIs) will be calculated for relative risk, as well as risk differences for categorical variables, and mean differences with 95% CIs will be calculated for continuous variables. We plan to analyze the partial data once annually during the recruitment of patients.

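### The gestational-age stratification announced in section 2.1 is carried into neither the allocation rule (2.5) nor the named analyses (2.13)

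*Protocol article*

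**What the plan says.** Section 2.1 (Study Design): "we will stratify the study group by gestational age into 24–28 and 29–32 weeks of gestation subgroups". The stated purpose is to make the findings more relevant. The sentence does not say whether the strata serve allocation, analysis or both.

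Section 2.5 (Randomization Criteria): "Enrolled infants will be randomized (1:1 allocation) with a block size of six". It gives ratio, timing and block size, and mentions no stratum.

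Section 2.13 (Statistical Analysis): "Categorical variables will be analyzed using either the chi-square test or Fisher’s exact test". Continuous variables get the t-test or the Wilcoxon rank-sum test. None of these tests uses a stratum.

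On prognosis, the Introduction links the frequency of late-onset sepsis to the degree of prematurity. Section 2.8.2 puts osteopenia at "approximately 20–30% of children with a birth weight < 1500 g and in 50–60% of children with a birth weight < 1000 g".

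**The concern.** A stratification factor does its work in two places: separate allocation lists, and a comparison made within strata. Here it is announced and then appears in neither. Someone who builds the list from section 2.5 alone would build a single blocked list. That keeps the arm totals within three of each other but leaves the split of 24–28 week infants to chance.

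At stake is the precision and face validity of the comparisons for which immaturity is prognostic. By the article's own account these are sepsis and, through birth weight, bone disease. Both are secondary outcomes, but both are named in the trial's aim. In a single-centre trial of 130 infants, a visible excess of very immature infants in one arm would make those results hard to read without adjustment.

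**Working it through.** **Inputs from the protocol article.** Blocks of six, 1:1 (2.5). Strata 24–28 and 29–32 weeks (2.1). From section 2.12: a control-arm rate of 80%, a reduction of 25% to be detected, 80% power at a 5% significance level, 54 infants per arm, and a total set at 130.

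**Assumption.** The share p of infants in the 24–28 week stratum is not given; the range used is 30–50%.

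**Step 1: the plan's own figure.** Read 25% as percentage points (80% vs 55%), two-sided, pooled variance, no continuity correction. The mean proportion is 0.675.

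n = [1.960·√(2·0.675·0.325) + 0.842·√(0.80·0.20 + 0.55·0.45)]² / 0.25² = (1.298 + 0.537)² / 0.0625 ≈ 53.9, so 54 per arm.

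The stated 54 reproduces, and nothing below changes it.

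**Step 2: chance gap with one list.** With 65 per arm and allocation unrelated to gestational age, the between-arm gap in the younger share has

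SD = √(2·p(1−p)/65) = √(4p(1−p)/130).

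- p = 0.3: √(0.84/130) = 8.0 points
- p = 0.4: √(0.96/130) = 8.6 points
- p = 0.5: √(1.00/130) = 8.8 points

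**Step 3: simulation of both schemes** (N = 130, permuted blocks of six, 40,000 trials per setting).

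| Younger share | One list: SD | Gap > 10 points | Gap > 15 points | Within strata: SD | Gap > 10 points |
|---|---|---|---|---|---|
| 30% | 8.0 | 21.2% | 6.3% | about 1.2–1.3 | 0% |
| 40% | 8.6 | 24.4% | 8.6% | about 1.2–1.3 | 0% |
| 50% | 8.8 | 25.4% | 9.5% | about 1.2–1.3 | 0% |

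With 108 infants (2 × 54), the one-list SD is 8.9–9.5 points and gaps of at least 10 points occur in 25–29% of trials.

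**Step 4: what a gap does to a secondary outcome (illustration only).** Take proxy risks of 55% and 25%, the midpoints of the section 2.8.2 ranges, a difference of 30 points.

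- A 10-point gap moves the unadjusted difference by 0.10 × 30 = 3 points; a 15-point gap moves it by 0.15 × 30 = 4.5 points.
- For scale, at an assumed overall risk of 40%, the standard error of the risk difference is √(2·0.4·0.6/65) = 8.6 points with 65 per arm and √(2·0.4·0.6/54) = 9.4 points with 54. The shift is therefore about a third to a half of one standard error.
- The part of the outcome variance that lies between strata is p(1−p)·0.30². At p = 0.5 it is 0.0225 of a total 0.40 × 0.60 = 0.24, or about 9%. On these proxies, that is the variance that using the strata removes.

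**The case against.** **Silence is not contradiction.** Section 2.5 does not say there is a single list. Read together with section 2.1, it is compatible with blocks of six inside each announced stratum, and an article condenses a fuller protocol. This stands in part. A reader might infer that the trial is in fact randomising without strata; the documents do not show that. What remains is that the one rule given for allocation, specific down to the block size, does not carry out the stratification announced four sections earlier.

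**Section 2.1 may mean subgroup reporting only.** That is possible, and simple blocked randomisation would then be valid. The text would still need to say so, and arm sizes within each subgroup would be left to chance. In a stratum of 39 infants (30% of 130), a split of 22 to 17 is a gap of 5/65, or about 8 points: one standard deviation.

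**Chance imbalance is not bias.** This stands in full. Randomisation remains valid, the type I error rate is not inflated, and the ordinary standard error already allows for such imbalance.

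**The illustration is soft.** This also stands. The birth-weight classes are nested (infants under 1000 g are also under 1500 g), they are not the gestational-age strata, and the figures describe osteopenia in general rather than the trial's biochemical definition. The true gap between strata is not in the article, and even on this proxy the shift is at most about half a standard error.

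**Conclusion.** The point holds as an unreconciled inconsistency with a modest, avoidable cost. If section 2.5 is followed as one list, the gap in the 24–28 week share has an SD of about 8–9 points at N = 130 and exceeds 10 points in roughly one trial in four or five. With blocks within strata the SD is about 1 point. These figures rest on the assumed 30–50% share.

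The cost is precision and credibility for sepsis and bone disease, which the article links to prematurity or low birth weight.

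Two stronger readings are tempting and unsupported. One is that the imbalance invalidates or biases the trial; it does not. The other is that it distorts the primary endpoint. The control dose depends on birth weight, so an indirect route is conceivable, but the article gives no weight-by-gestation data and nothing on how gestational age predicts 25(OH)D status at 28 days. The sample size is unaffected.

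**What to change.** 1. Reconcile sections 2.1 and 2.5. In 2.5 state: 

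   *Infants are randomised 1:1 in permuted blocks within each of two gestational-age strata (24–28 and 29–32 weeks), with a separate list for each stratum.* 

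   Gestational age is an eligibility criterion, so it is known at randomisation.

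2. In section 2.13 use the strata in the comparison, for example a Cochran–Mantel–Haenszel risk difference and relative risk with 95% confidence intervals. Without this, stratified allocation would be analysed with a standard error that ignores it and is slightly too large.

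3. If recruitment is already running on a single list, keep that list and adjust for gestational-age stratum in the analysis. Changing the allocation scheme mid-trial carries its own risk and is not needed, because adjustment recovers most of the precision.

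4. If section 2.1 was meant only for subgroup reporting, say so there, and still adjust for stratum.

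Cost: one sentence in each section, a second list, one extra incomplete block (at most three infants of imbalance per stratum) and slightly more analysis work.
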